**Ethics and dissemination:**

This study has been approved by the St Vincent’s ethics committee (approval no. LRR 177/21). All participants will complete a written informed consent prior to enrolment in the study. The study results will be disseminated widely *via* local and international health conferences and peer-reviewed publications.

## Background

1.

Congestive heart failure (CHF) causes significant morbidity and mortality. At least 50% of patients have one or more comorbid conditions such as type II diabetes, coronary heart disease, chronic kidney disease, hypertension, and others. Patients diagnosed with CHF take multiple medications and prescribed complex treatment regimens. Good health literacy is needed to action diet, complex self-management skills, and maintain compliance life-long (1, 2). In addition, interacting effectively with health systems is required for lifestyle maintenance, behavioural changes, and consolidation of chronic disease self-management (CDSM). Patients and health system factors can act as barriers to optimal care, including developing new comorbidities, geography (isolation and remoteness), language, culture, education and socio-economic disadvantage, social supports, and negative attitudes towards establishments (3). Hospital readmissions are high, with 25–50% occurring within 1–6 months of discharge; this largest cost contributor is also preventable and amenable, as studies have demonstrated the care process (4). Better healthcare delivery systems could be achieved by the addition of patient self-management capabilities within programmes that meet patient needs and link health services (4, 5).

Chronic disease management and CHF programmes share similar care domains, one aspect is CDSM. Despite setbacks, there is optimism that CDSM will provide increasing importance to CHF programmes. Nevertheless, to an increasing extent, translational issues such as the containment of resource utilisation and cost blowouts must be factored into the aims of CDSM. These are, however, not the primary aims of large randomised controlled trials. These translational issues are better understood when exploring a patient’s journey. When patients seek health services, the acuity determines if interactions are in the community or *via* acute services such as ambulance, emergency, and hospital admissions. Following acute care, patients then transition back to the community. This process creates new information, new members of a health team, and may also create silos. There are CHF patients that inadvertently utilise the acute pathways and are potentially preventable admissions. It is thus vital that CDSM research aligns with clinical and administrative realities.

To acquire and action CDSM, most generic frameworks have three tiers: (a) four goals: performance mastery, modelling, interpretation of symptoms, and social persuasion; (b) three tasks: medical management, role management, and emotional management; and (c) five skills: problem solving, decision-making, resource utilisation, forming a patient–healthcare provider partnership, and taking action (3, 6–11). Models, processes, and systems of care are pathways to delivering disease management programmes (5). In theory, CDSM should assist these programmes; however, structural deficiencies exist for CHF. Nonetheless, tremendous gains have been documented with CDSM (1, 2, 12), disease management (13–17), and performance improvement strategies (1, 2, 4).

In relation to gaps that need attention, heterogenous patient populations, clinical scenarios and “one shoe fit all” models are important examples (11). In this context, programmes that balance comprehensiveness by identifying unique client problems set goals to complement guideline-based care with resources (7–9, 11, 13), link to broader health channels, and finally, contribute to risk stratification and readmission reduction will contribute to CDSM usefulness. On the latter, triaging CHF can be time-consuming and resource-intensive (10). CDSM programmes should also target this as an important performance measure. The *Self-management in Heart Failure Study (SELFMAN-HF) and Screening in Heart Failure risk stratification tool (SCRinHF)* explore these issues and are described in more detail.

## Methods

2.

### Aim and scientific hypotheses

2.1.

The *Self-management in Heart Failure Study* assesses the feasibility and validity of a short form *SCRinHF* tool (6), with the established comprehensive *Flinders Program of Chronic Disease Self-management* (Flinders Program or CFPI) (18–21) for participants who were prescribed an SGLT-2 Inhibitor for CHF. In this, we hypothesise: first, guideline level of care as established by Ref. (1, 2, 12–17), and CDSM can be used to enhance the delivery and uptake of guideline-based care (22–26); second, to achieve this, we have to define clinical pathways. In this study, the model of care is based on patients utilising community cardiologists with community-based triage (Figure 1); third, a short form CDSM tool (*SCRinHF*) will improve efficiency in delivering CDSM programmes without compromising clinical outcomes as compared to the CFPI (Figure 2). The *SELFMAN-HF* study thus aims:

To examine the relationship between CDSM and CHF-related health outcomes over a 12-month period. The CDSM tools that will be used are the CFPI and SCRinHF (Table 1). The study will establish the feasibility of use and the concurrent and predictive validity of the SCRinHF when compared to the CFPI in predicting self-management, clinical measures, and predictive measures of health outcomes (hospital readmissions) in CHF and their limitations and strength

**Figure 1 fig1:**
[figure not shown]
Patient journey pathway, challenges, and opportunities for heart failure.

**Figure 2 fig2:**
[figure not shown]
Summary of standardisation structures for evidence and clinical services. **(A)** Heart failure structures for clinical standards, taxonomy domains to build systems, research methodologies to gain evidence that eventually lead to guidelines. The subsequent steps are observations on: Phase 4 translation to trial type populations, cost-effectiveness to the general population; Phase 5 is a newly coined term to explore logistics in service delivery; the final point are unknowns such as vulnerable populations, new findings that require a bench to bedside approach of gathering evidence and testing these hypotheses in a Phase 3 randomised trial. Population level. RCT – randomised controlled trial [adapted from references (1, 2, 12–16)]. **(B)** Chronic disease self-management is standardised around the Flinders Program of Chronic Disease Condition Management (CFPI). Partners in Health (PIH) are 12 self-rated questionnaire patient complete to assess self-management knowledge, attitudes, behaviours, and impacts of their chronic condition; Cue and Response Interview (C&R) is administered by health workers using an open-ended dialogue on the same questions as the PIH, and rated from the health workers perspective, and shared with the patient; Problem and Goals assessment (P&G) is health worker tool utilising behavioural psychotherapy, open-ended questions negotiate patient-identified problems and formulate goals to address them; care plan records and scores behavioural changes, monitors and progressively implements at patients pace. Barriers, strengths, and priorities identified through PIH, C&R, and P&G are incorporated into fully negotiated care plans [adapted from reference (11)]; the SCRinHF tool extracts and focuses on five domains from the CFPI. As it is a screening tool, domains tested can be re-explored should a patient be identified as at high risk and require more intensive support.

**Table 1 tab1:** SCRinHF heart failure readmission risk scoring tool.

Domains of care	Heart failure ambulatory readmission risk dimensions of care	#Yes	No	*D
1. Baseline readmission risk	Comorbid risk [Ref (1–3)]	1–3+	0	
	Managing ADL	1	0	
	Adequate Social supports	1	0	
	Compliance	1	0	
	Mood – neurovegetative, psychological [Ref (4)]	1	0	
2. Living at home (skills & goals) Self-care maintenance Self-care management Self-care confidence/efficacy	a. Do you know “how to (skill).to achieve (goal)”… [Ref (5, 6)]			
	Problem solve – e.g. (i) monitoring;	0 or −1	1	
	Decision making question	0 or −1	1	
	About physical function – e.g. (i) exercise	0 or −1	1	
	b. Do you know “what to do if (skill) to achieve (goal)”…			
	Resource utilisation, e.g., (i) monitoring with action	0 or −1	1	
	Form patient provider partnership, e.g., (i) engage health system	0 or −1	1	
	Action planning when self-tailoring	0 or −1	1	
	c. Do you know “how confident you are (skill)…when faced with (goal)”			
	Has client previously received Rehab/education? State level of Self-Care Confidence (SR, SE, TI, TE) – e.g. (i) adherence to diet (ii) compliance	0 or −1	1	
3. Supports for living at home	Do you need additional services [Ref (7–10)]	0 or −1	1	
4. Chronology	Presentation of CHF or comorbidity acute (1) or subacute-chronic (0). (If acute go to long-form; cood with inpt team).	1	0	
5. TOTAL SCORE (NB// minus score given if excellent self-care capacity or support)				
6. HF Team (HFT)	15. Correspondence to: (dn, gp, ot, n, p, ph, r, shf, so, others)			
Service delivery needs				
Score ≤ 1 in each dimension or requires < 1 domain of care	Score = 2 in at least 2 or more for any dimension or > 1 domain of care	Score ≥ 3 for any dimension or > 2 for a dimension or domain of care		
Patient has low re-admission risk and can self-manage. Reassess bi-annually	Patient has moderate readmission risk and may have limited self-care capability	Patient is likely to be a high risk of readmission and probably does not have capacity to self-care independently		
Short-term allied health support and self-care education may be appropriate. Patient may be a good candidate for technology-assisted out-patient HF programs	Medium to long-term allied health support and self-care education may be appropriate. Patient may be a candidate for technology-assisted out-patient HF programs	Long-term allied health support and nurse-led out-patient support are likely to be needed. Patient is unlikely to independently self-care.		
Tailored resources required				
Domain combinations (C; H; T)	Dimension hierarchy (R; S; A)	Duration: (S; M; L)	Notes: -Intervention Model (I) - Other consideration	
1. 2.				

SCRinHF tool previously published (6). Abbreviations and operating manual refer to Supplementary Appendix.

## Study objectives

3.

The *SELFMAN-HF tests the feasibility and validity of the SCRinHF tool,* comparing the novel one-page tool to the gold standard Flinders Program of Chronic Condition Self-management Tool (CFPI). Feasibility: there are no prior comparisons of short and long form CDSM tools applied to CHF. Validity: first, this will explore comparisons of the SCRinHF to the CFPI in a range of measures including, self-management, clinical progress, and predicting 12 months major cardiovascular outcomes including readmission; and second, the Delphi method to attain peer acceptability and expert consensus on the *SCRinHF* tool.

## Patient cohort and selection criteria

4.

A minimum of 40 patients with CHF who meet the inclusion criteria will be offered an opportunity to participate. In uncertain cases, subjects will be considered eligible if the review of medical records demonstrates that they have a CHF diagnosis based on ACC/AHA and National Health Data Dictionary standardised definitions (1, 2). The project physicians will perform this. An independent physician will review uncertain cases.

Eligible patients will be: aged over 18 years; able and willing to provide informed consent; started SGLT-2i within 6 months - for systolic HF (echocardiographic EF <40%); receive one aspect of CHF care within a defined study health corridor.Patients will be excluded: If concerns are raised by any medical staff, the patient has a life expectancy of ≤6 months whilst receiving palliative or nursing home care. Cognitive status and dementia will not be a contraindication if there is consent from a caring relative or legal guardian and the ability to complete the CFPI; have a significant neurological/cognitive impairment or are unable for any reason to provide written informed consent; do not usually reside within the region (or for whom no follow-up data can be obtained); started SGLT2-i for more the >6 months.*Health Staff* will be sent surveys if they manage chronic diseases, including CHF and are willing to complete an Assessment of Chronic Illness Care (ACIC) questionnaire.

## Study design

5.

### Study objectives, measures, and endpoints

5.1.

The *SELFMAN-HF* is a prospective, observational case-cohort study, in three phases: *Phase 1,* is defining the geographical boundaries of the community cardiology clinic in Western Melbourne, Australia, *and the* development of appropriate clinical indicators, study design, and registry; *Phase 2,* is the assessment of data and recommendations; and Phase 3, the Delphi methodology process. The measures and endpoints are highlighted for each sub-section.

### Study mapping, development of appropriate clinical indicators, study design, and registry (Phase 1)

5.2.

The geographical area was defined *via* an internet search, supplemented by direct communication with local council health agencies and Victorian state tertiary hospital jurisdictions. We reviewed publications within our group, the heart foundation, CSANZ and European and American Cardiac societies for self-management tools, readmission risk factors, and chronic disease assessment tools. As these areas have been greatly studied, we felt it reasonable to use consensus works as the foundation principles to consolidate and build from. The Krumholtz taxonomy of chronic disease management (12), Flinders Program of chronic disease self-management or CFPI (6–8), and established chronic condition assessment tools* will be used to standardise data collection (1, 2, 5, 11–16) and recording through the service channels [*previously published in Tables 1–3 in Iyngkaran et al. (3)].

### Assessment of study data, measures, recommendations, and intervention (Phase 2)

5.3.

Details of the CFPI, heart foundation cardiovascular chronic disease tools, and patient assessment and chronic illness care satisfaction questionnaire (PACIC) are previously summarised [Table 3 in Iyngkaran et al. (3)] and published (3, 7, 8, 11). The CFPI tool and PACIC will be used to obtain information on patients’ CDSM capacity and patient satisfaction informing the CHF journey over 12 months. The PACIC is in three parts, where self-management assumes a component of the third category. Other study measures include the assessment of participants’ clinical changes in CHF and general wellbeing through the 6-month CFPI score, NYHA class, MLWF and 6MWT, and plasma NT-proBNP (Figure 3). Data on readmissions and mortality will be obtained from patient interviews and, if possible, healthcare records from main health providers, hospitals, primary healthcare (PHC) records, and community cardiac services. Cost–benefit analysis will be determined using standard billing criteria for public hospital funding Medicare Australia. These data will be compared with any ongoing prospective works on the CHF patient journey in Victoria. All enrolled patients will receive routine medical care as per Heart Foundation guidelines 2018 (27, 28). No additional investigations will be required from usual care. Comparing the long form CFPI and short form (*SCRinHF* tool) – trained staff who administer the CFPI will record the time to complete the process. The *SCRinHF* tool (Table 1) will be completed by an independent staff from those who filled in the CFPI. They are blinded to patients and will receive access to raw data on patients. The time to complete this will also be recorded.

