### End points

5.9.

The study endpoints for each phase are: Phase 1 – documentation of health journeys of patients; Phase 2 – interrogation of CFPI and SCRinHF tools for self-management capabilities and readmission risks; and Phase 3 – all data will be accumulated and discussed in the Delphi process. The primary endpoint is the readmission risk as scored by CFPI and SCRinHF and the correlation between the two tools. In addition, the following data will be collected: detailed maps of individual patient journeys and a patient and staff questionnaire on the process. Validation and times to complete the short and long forms will be recorded. The primary endpoint is 80% concordance in MACE and medical events between CFPI and SCRinHF tools. Secondary endpoints are data for cost analysis, and to inform the focus group in planning an RCT for efficacy, validity, reliability, and variability.

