### Expected outcomes

5.12.

The primary outcomes are to achieve concordance in readmission risk between CFPI and SCRinHF, and the number of patient readmissions to the hospital. The secondary outcome is to achieve convergent validity between CFPI and SCRinHF and potential economic cost benefits using the SCRinHF tool.

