### Randomisation/blinding

5.13.

Not applicable for Phases 1–3. Trained study staff completing the SCRinHF tool will have access to raw patient data, but be blinded to the patient when completing the tool. Following Phase 3, a focus group will convene to finalise the SCRinHF trial and study tool. Randomisation strategies will be a priority for any future studies.

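### The stated costing method (hospital and Medicare billing) cannot attribute an economic benefit to SCRinHF rather than CFPI; the completion times already recorded could support a comparison but are not linked to the costing

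*Protocol article*

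**What the plan says.** All references are to the protocol article.

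- **Outcome.** Section 5.12 includes in the secondary outcome "potential economic cost benefits using the SCRinHF tool". Section 5.9 puts the economic element more loosely: "Secondary endpoints are data for cost analysis, and to inform the focus group in planning an RCT".
- **Costing method.** Section 5.3 says the cost-benefit analysis "will be determined using standard billing criteria for public hospital funding Medicare Australia". No other costing method appears. The next sentence says the data will be set against other prospective studies of the heart failure patient journey in Victoria, which are not identified.
- **Design.** Under section 5.1 the study "is a prospective, observational case-cohort study, in three phases". On randomisation, section 5.13 says "Not applicable for Phases 1–3". Section 5.3 gives all enrolled patients the same usual guideline care.
- **How the tools are completed.** Trained staff administer the CFPI. The SCRinHF form "will be completed by an independent staff from those who filled in the CFPI", and of those staff section 5.3 says: "They are blinded to patients and will receive access to raw data on patients".
- **Time.** Section 5.3 has completion time recorded for each tool, and section 5.9 repeats this: "Validation and times to complete the short and long forms will be recorded". Neither section says that the times enter the cost analysis.

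**The concern.** The outcome is a benefit of using one tool, while the method measures what patients' care cost. These match only if using SCRinHF, as opposed to CFPI, could change the care that is billed, and if the design could show such a change. The design as described provides for neither.

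Two things are at stake. First, a billing total from this cohort could be carried into RCT planning as if it said something about SCRinHF. Second, the efficiency advantage the tool was built for would go uncosted. Section 2.1 hypothesises more efficient programme delivery, and the Discussion gives the burden of traditional tools as the reason for a one-page form. The costing sentence does not mention staff time, where that advantage would appear.

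**Working it through.** The article states no cost, cost difference or variance for this outcome, so there is no figure to reproduce. The check is whether each available quantity can separate the two tools.

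**1. Billed cost within the cohort.** Let C_i be the hospital and Medicare cost billed for patient i. With both forms completed on the same patient, there is one C_i, and it is not indexed by tool. No group is managed with SCRinHF alone, with CFPI alone or with neither. SCRinHF is scored from data by staff blinded to the patient, and nothing in the article says that its score alters care. So C_i carries no information on the effect of using one tool instead of the other. A larger sample does not change this.

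**2. Billed cost against other Victorian studies.** The contrast is (mean cost in this cohort) − (mean cost elsewhere). Both tools are completed in this cohort, so even a perfectly matched outside cohort would give the combined setting, not SCRinHF. A difference would be at least as attributable to the CFPI, which is administered to patients and leads to negotiated care plans (Figure 2 legend).

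**3. Billed cost by risk band.** Let H_S and H_F be the patients placed at high risk by SCRinHF and CFPI. Then

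Σ C_i over H_S − Σ C_i over H_F = (cost of patients high on SCRinHF only) − (cost of patients high on CFPI only).

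This can differ from zero, so billing can describe how each tool sorts costly patients. To turn it into a saving one must multiply by the fraction of cost avoided when someone acts on the classification. The design cannot estimate that fraction, so any result is a model resting on an outside assumption.

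**4. Staff time.** This quantity is indexed by tool. For patient i,

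D_i = w × [T_CFPI,i − (T_SCR,i + T_data,i)],

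where w is the staff pay rate, T_CFPI and T_SCR are the recorded completion times, and T_data is the time to collect the raw data that SCRinHF is filled from.

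| Input | Source | Value |
|---|---|---|
| T_CFPI | Discussion, for traditional tools generally | 45–60 min, if it applies to CFPI (assumption) |
| T_SCR | not given | unknown |
| T_data | not given | unknown |
| w | not given | unknown |
| Patients | section 4, minimum | 40 |

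Only a ceiling follows. If T_SCR + T_data were zero, the saving would be 45–60 min per patient, or 40 × 45 / 60 = 30 to 40 × 60 / 60 = 40 staff hours over 40 patients. The true saving is smaller by T_SCR + T_data. If collecting the data takes as long as the CFPI does, nothing is saved. No point estimate is possible.

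**The case against.** The strongest defence has four parts.

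- **The costing sentence is not a tool-versus-tool comparison.** It is followed by the external Victorian comparison, and the comparison of long and short forms begins separately afterwards. A reader might infer that the plan calls for a paired SCRinHF-minus-CFPI difference in billing that must be exactly zero. The document does not support that: no such difference is specified anywhere. This part stands. What remains is that the external comparison cannot isolate SCRinHF either.
- **Billing can inform a potential benefit.** A reader might infer that billing data are useless for this outcome. That is too strong, as step 3 of the working shows. Costs by risk band are informative and could feed a model. This stands, but the article describes no such model, and its result would not be causal.
- **The claim is modest.** Section 5.12 speaks only of a potential benefit, section 5.9 speaks of data for a cost analysis and for planning an RCT, and the Discussion calls the design hypothesis generating. This stands and lowers the weight of the point.
- **Cost inputs and unit prices are detail that an article leaves out.** This stands for the pay rate, and billing criteria might even be used to price staff time, though the text does not say so. It does not answer the main point: the article fixes a method and an outcome that do not match, and more billing detail cannot create a contrast that the design lacks.

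A reader might also want a figure for the hours saved. Assuming 10–20 min for SCRinHF gives (45 − 20) to (60 − 10) = 25–50 min per patient, or about 17–33 hours over 40 patients. The documents do not support it: the SCRinHF time is invented, the 45–60 min is not specific to CFPI, and T_data is left out.

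**Conclusion.** The point holds in a limited form. Billed hospital and Medicare cost cannot be attributed to SCRinHF rather than CFPI in this study, whether viewed within the cohort or against other Victorian studies. It can describe cohort cost, or support a modelled, non-causal estimate by risk band. The conclusion does not extend to everything collected, since the recorded completion times can support a real comparison of the tools.

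It rests on two readings. That both tools are completed on the same patients is the plain sense of sections 5.3 and 5.9, not a verbatim statement. That the SCRinHF score does not direct care is inferred from the article never saying that it does.

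The size of the time saving is unknown. Severity is minor: the outcome is secondary and exploratory, and neither the primary endpoint nor the recording of completion times and billing is affected.

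**What to change.** - **Sections 5.3 and 5.12.** Define the within-study SCRinHF versus CFPI cost outcome as the paired difference in assessment cost: recorded completion time multiplied by a staff pay rate. The SCRinHF side should include the time to collect the data it is filled from. State how time is divided if the same data collection serves both tools.
- **Billed costs.** Report them descriptively, for the whole cohort and by each tool's risk band, as input to the future RCT. Do not present them, or their comparison with other Victorian studies, as a benefit of SCRinHF. The article shows bands only for SCRinHF (Table 1), so the CFPI grouping should be stated.
- **Downstream benefit.** Leave any effect on readmission cost to the planned RCT, or label it as modelled and give its assumptions.

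The cost is a wording change, a pay rate and, if it is not already captured, a note of data-collection time. No new patients or visits are needed. The downside is a narrower economic claim.

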### Study population/ recruitment of subjects / setting

5.5.

The study setting of Western Melbourne defined the catchment although recruitment will only take place at community cardiology outpatients and support services for CHF. Recruitment will occur over a 6-month period. Patients identified will be referred to the study case manager for consent, and thetime will then be arranged to review the CFPI, PHQ-9, MLHF, and PACIC. Baseline demographics, tests, and questionnaire scores (Figure 3) will be recorded. All staff will be healthcare workers within community cardiology and aligned services. Participants will be recruited over a 12-month period, from September 2021 to September 2022, and followed for 12 months, ending September 2023. Health staff from primary and tertiary care managing CHF patients will be approached to complete the ACIC, between September 2021 and September 2022.

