A strength of this study is the ability of the observational sample size to inform a future randomised study, by the event rates anticipated with the CHF inclusion criteria (LVEF <40%). In Australia, an SGLT-2i can be provided to all patients with NYHA class II and LVEF <40%; thus, its use requires a standardised baseline, and it requires education on self-management to use it safely. In addition, we were also able to leverage on previous works which established performance measures (5, 12, 13, 15, 16, 29) some updated (14), to inform and extract parameters for this study.

An important limitation in study-specific tools is questionnaires that have qualitative and quantitative components [Tables 2, 3 previously published (3)]. The frameworks for CDSM and CPFI (11) have been previously detailed. These goals (11, 19–21) and established CHF readmission risk scores were foundations on which the SCRinHF tool was modelled. The limitations of traditional tools, including patient fatigue (45–60 min to complete), were the impetus for the development of a one-page tool; overlaps in questions between tools and investigators were the motivation to train end users to populate other tools with overlapping questions where appropriate [previously published Table 2 Iyngkaran et al. (3)]. Monitoring clinical changes with CHF is also important. The balance between quick and less accurate assessments such as NYHA classification, general chronic disease scores, and CHF-specific scores can impact clinical standardisation and require thoughtful considerations (30–34). These points will also be factored in when informing a larger definitive RCT.

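### SCRinHF is scored from raw data not stated to exclude CFPI responses, so concordance is open to shared-source bias of unknown size, and the two completion times measure different tasks

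*Protocol article*

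**What the plan says.** All references are to the protocol article.

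- **Who scores.** Section 5.3 says SCRinHF "will be completed by an independent staff from those who filled in the CFPI".
- **From what.** Of these staff the same section says "They are blinded to patients and will receive access to raw data on patients". Section 5.13 repeats the rule: "Trained study staff completing the SCRinHF tool will have access to raw patient data, but be blinded to the patient when completing the tool".
- **What the patient is asked.** Section 5.5 describes a session after consent, for which time "will then be arranged to review the CFPI, PHQ-9, MLHF, and PACIC". SCRinHF is not on that list.
- **How the tools relate.** The Figure 2 legend says "the SCRinHF tool extracts and focuses on five domains from the CFPI". It also says of one CFPI component that the "Cue and Response Interview (C&R) is administered by health workers using an open-ended dialogue".
- **Overlap between tools.** The Discussion says that overlapping questions were a motivation to "train end users to populate other tools with overlapping questions where appropriate".
- **Sources and times.** Section 5.3 names the CFPI and PACIC as the means of learning patients' self-management capacity. It has staff record the time taken to administer the CFPI and the time taken to complete SCRinHF.
- **Endpoint.** Section 5.9 gives 80% concordance between the two tools as a primary endpoint.

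**The concern.** An agreement study needs each tool to collect its own information. Here the SCRinHF rater does not meet the patient, so each answer must come from something already on file. Where the only file entry on a self-management item is the patient's CFPI response, the two tools share that response and any error in it. Agreement then partly reflects the common source.

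Two results are at stake. The first is concordance, which the article treats as primary and which feeds the Delphi process and the planning of an RCT. The second is the time saving, which bears on the hypothesis in section 2.1 that the short form makes self-management programmes more efficient to deliver. Both would lean in favour of SCRinHF.

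**Working it through.** **1. How much of SCRinHF needs the patient.** Scored rows in Table 1:

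| Domain | Scored rows | Put to the patient as questions |
|---|---|---|
| 1 Baseline risk | 5 | 0 |
| 2 Living at home | 7 | 7 |
| 3 Supports | 1 | 1 |
| 4 Chronology | 1 | 0 |
| Total | 14 | 8 |

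That is 8/14 = 57%, or about half.

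**2. Where those answers could come from.** Section 5.6 collects comorbidities, social support, diet, physical activity and PHQ-9. These can serve several Domain 1 rows. They do not plainly cover problem solving, action planning or confidence. For self-management capacity, section 5.3 names two instruments, the CFPI and PACIC. It describes self-management as only one component of the third part of PACIC. The CFPI is thus a main candidate source for the eight rows, and nothing in sections 5.3 or 5.13 withholds it.

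**3. The plan's own figure.** The 80% target has no derivation, so there is nothing to reproduce. For scale, 80% of the minimum 40 patients is 32. The 95% interval for 32/40 is 65% to 90% (Wilson) or 64% to 91% (exact).

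**4. Illustration of the bias. Every input is assumed.** Let c be agreement when the tools are given separately and f the share of patients whose classification is fixed by shared data. Then observed agreement = f + (1 − f) × c.

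- c = 0.60, f = 0.50: 0.50 + 0.50 × 0.60 = 0.80.
- c = 0.65: f needed for 0.80 is (0.80 − 0.65)/(1 − 0.65) = 0.43.

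Observed agreement, with the binomial chance of at least 32/40 in brackets:

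| c | f = 0 | f = 0.25 | f = 0.50 | f = 0.75 |
|---|---|---|---|---|
| 0.50 | 0.50 (<0.001) | 0.625 (0.014) | 0.75 (0.30) | 0.875 (0.945) |
| 0.60 | 0.60 (0.006) | 0.70 (0.11) | 0.80 (0.59) | 0.90 (0.985) |
| 0.70 | 0.70 (0.11) | 0.775 (0.44) | 0.85 (0.865) | 0.925 (0.998) |

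This formula counts every affected patient as agreeing, so it gives the bias at full strength. A gentler check shares items, not classifications. It simulates 14 yes/no items per tool, a standard normal trait, tool-specific error with SD 0.7, item error with SD 1, and three categories cut at total scores of 4 and 9. Agreement is 55% with no shared answers and 71% with 7 of 14 shared. The direction is the same. The simulation gives both tools the same items and cut-offs, which the real tools do not have, so it is also only an illustration.

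**5. The times side by side.** CFPI time is recorded by the staff who administer it, and the process includes an open-ended interview. SCRinHF time is recorded by staff without patient contact, working from data that others collected. The second time omits the collection step that the first includes. This follows from section 5.3 whatever the raw data contain.

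**The case against.** - **Independent raters.** SCRinHF staff are not the CFPI staff. This stands as a real safeguard against one rater carrying a judgement from one form to the other. It does not remove a shared source.
- **Raw data are undefined.** A reader might infer that SCRinHF is filled in from CFPI forms and that agreement is guaranteed. The article does not say so. An operating manual is placed in an appendix that is not shown, and other data are collected. The tools also score differently, so shared inputs need not give the same category. Only exposure to bias is supported.
- **Carry-over of answers.** A reader might infer that CFPI answers are copied into SCRinHF. The Discussion sentence concerns tools in general, with a qualifier, and does not name this pair.
- **Interview length.** It is tempting to set SCRinHF time against a 45–60 minute CFPI interview. The Discussion gives that range for traditional tools, not for the CFPI specifically.
- **Outcome contamination.** A reader might infer that predictive validity is compromised. That depends on when SCRinHF is scored, which the article does not state. Comparison with observed readmissions is not affected in the same way as concordance with the CFPI.
- **Overlap is natural.** A short form drawn from its long form should share content. That is right: the fault lies in possibly shared responses, not in shared domains.
- **Feasibility study.** The article calls the work hypothesis-generating and its scoring untested. This tempers the claims, but the stated limitations do not mention a shared source or the mismatch in timing.

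**Conclusion.** The point holds as exposure to bias. Followed as written, the plan lets SCRinHF raters use whatever is on file for about half of the items, with the CFPI a main named source and no stated exclusion of CFPI responses or later events. Concordance may therefore be too high by an amount the document does not allow anyone to calculate. A result of 80% would not show that a one-page screen given on its own agrees with the CFPI. The rise from 60% to 80% rests wholly on the assumption that half of the classifications are fixed by shared data.

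The timing point is firmer and needs no such assumption: the two recorded times cover different tasks and cannot be set against each other as evidence of efficiency.

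**What to change.** 1. Define the raw data. Give SCRinHF raters a baseline-only extract without CFPI scores, risk ratings, care plans or post-baseline events.
2. State that answers are not carried over between the CFPI and SCRinHF.
3. Score SCRinHF before outcomes are known, or masked to them, and record the scoring date.
4. List the items that can be answered only from CFPI responses. For patients still to have a baseline assessment, ask these items separately and state the order, since either tool could prime the other. For all others, report concordance with and without these items, and describe it as agreement from shared source data.
5. Report SCRinHF time as scoring time from records, and do not compare it with CFPI administration time to claim efficiency.

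**Cost.** The extract, masking and relabelling are cheap. Asking patients directly may no longer be possible: sections 5.5 and 5.14 put the end of recruitment at September 2022, and the article appeared in May 2023. The fallback in step 4 is therefore needed. The price is probably a lower concordance figure and a weaker time-saving claim.
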